## Abstract

**Background:**

Mobile phone technologies including SMS (short message service) have been used to improve the delivery of health services in many countries. However, data on the effects of mobile health technology on patient outcomes in resource-limited settings are limited. The aim of this study therefore is to measure the impact of a mobile phone SMS service on treatment success of newly diagnosed type 2 diabetes in an urban area of Bangladesh.

**Methods/design:**

This is a single-centred randomized controlled intervention trial (prospective) comparing standard-of-care with standard-of-care plus a mobile phone-based SMS intervention for 6 months. A total of 216 participants with newly diagnosed type 2 diabetes will be recruited. Data will be collected at the outpatient department of Bangladesh Institute of Health Science (BIHS) hospital at baseline and after 6 months. The primary outcome measure will be change in HbA1c between baseline and 6 months. The secondary outcome measures are self-reported medication adherence, clinic attendance, self-reported adoption of healthy behaviours, diabetes knowledge, quality of life and cost effectiveness of the SMS intervention. The inclusion criteria will be as follows: diagnosed as patients with type 2 diabetes by the BIHS physician, using oral medication therapy, living in Dhaka city, registered with the BIHS hospital, using a mobile phone, willing to return for follow up after 6 months and providing written informed consent. Participants will be allocated to control and intervention arms after recruitment using a randomization software. Data will be collected on socio-demographic and economic information, mobile phone use and habits, knowledge of prevention, management and complications of diabetes, self-perceived quality of life assessment, self-reported diseases, medical history, family history of diseases, medication history, medication adherence, health seeking behaviour, tobacco use, physical activity, diet, mental health status, life events and disability, anthropometric measurements of weight, height, blood pressure and blood tests for HbA1c.

**Discussion:**

Mobile phone SMS services have the potential to communicate with diabetes patients and to build awareness about the disease, improve self-management and avoid complications also in resource-limited setting. If this intervention proves to be efficient and cost-effective in the current trial, large-scale implementation could be undertaken.

**Trial registration:**

DRKS00005188.

## Background

Diabetes mellitus, particularly type 2, is one of the most significant public health challenges of the 21^st^ century. More than 80% of diabetes related deaths occur in developing countries [1]. It is estimated that about 8.4 million people living in Bangladesh are suffering from diabetes already and by 2030, that number is expected to double, placing Bangladesh among the top five countries in terms of the absolute number of people living with diabetes [2]. Population data support an increasing trend in diabetes prevalence in Bangladesh, especially in urban areas where the prevalence is 8.1% compared to 2.3% in rural areas [3].

Non-adherence rates for therapies of chronic illness and for lifestyle changes are high with estimates ranging from 36% to 93% and averaging only 50% in developed countries [4,5]. Lack of adherence often leads to increased use of healthcare services, poor quality of life and increased healthcare costs [6,7]. In Bangladesh, adherence to medication is low due to several complex issues along with poor clinic attendance. This often leads to insufficient glycaemic control and avoidable life threatening complications. A recent study among newly diagnosed type 2 diabetes in Bangladesh reported 84% of patients had average to poor basic knowledge about their disease [8].

Mobile phone interventions for health are an emerging, rapidly-evolving practice and have been used to improve delivery of health services in many countries of the world [9]. Mobile phones can be a low cost solution to provide health education and increase adherence to treatment for people with chronic diseases like diabetes [10]. A study using mobile phone SMS by nurses in Korea found that SMS for 6 months reduced HbA1C in diabetic patients to 1.15% at 3 months and 1.05% at 6 months compared with baseline in the intervention group [11]. Mobile phone SMS have been shown to be an effective tool for providing diabetes health education, clinic and appointment reminders, medication reminders and for building awareness about the disease [12-14]. However, no data on the effects of such an approach on patient outcomes in resource-limited settings are available to date.

### Research objectives

The objectives of this study are to:1) Study the effect of mobile phone SMS on medication adherence and control of newly-diagnosed type 2 diabetes in an urban area of Bangladesh; 2) Test the use of mobile phone SMS as clinic appointment reminders and for building awareness about diabetes and its complications; 3) Measure the impact of mobile phone SMS on quality of life of diabetes patients in Bangladesh and 4) Evaluate the cost effectiveness of a mobile phone SMS intervention.

The results of the study will help the policy-makers to understand the importance of creating healthcare systems that better meets the needs of people and develop prevention and management strategies for diabetes and other chronic disease using innovative mobile phone technologies at the national level which can be replicated in other developing countries as well.

### Hypothesis

Our primary hypothesis is that mobile phone SMS intervention is superior in reducing HbA1c in newly diagnosed type 2 diabetes compared to standard care. Secondary hypothesis is mobile phone SMS will increase diabetes knowledge, medication adherence and clinic attendance better in the interventions group than in the control group. The third hypothesis is participants in the mobile phone SMS group will have a better quality of life than participants in the control group. The fourth hypothesis is that mobile phone SMS will be a cost-effective measure for glycaemic control.

## Methods/Design

### Study site and population

This study will be implemented at a Bangladesh Institute of Health Sciences (BIHS) Hospital Out Patient Department (OPD) in Mirpur, Dhaka city which is an affiliate organization of Diabetic Association of Bangladesh (DAB). The total number of diabetic patients receiving services from the BIHS Hospital OPD from July 2010 to June 2011 was 90,146 with 2026 new registrations and total 693251 tests performed in the laboratory of the Department of Biochemistry. The average number of patients per day in the BIHS OPD will be sufficient to cover the total sample size of this study in a short period of time. We will limit our data collection to this single center where the participants represent urban areas of Dhaka and Bangladesh. Consecutive patients from this center who meet the eligibility criteria will be asked to participate in the study.

### Study type

We will conduct a randomized controlled trial , comparing [1] standard-of- care (n = 108) with [2] standard-of-care plus a mobile phone-based SMS intervention (n = 108) for 6 months among patients with newly diagnosed type 2 diabetes receiving treatment at the OPD of BIHS hospital in Dhaka City (Figure 1).

**Figure 1 Fig1:**
[figure not shown]
**Flow chart.** Flow chart of study participants in the trial.

### Sample size

Assuming that standard care with metformin reduces HbA1c by 1% on average and the intervention adds another 0,5% [15,16]. Assuming a SD of 1, which seems reasonable and an alpha error level of 5%, the two-tailed calculation gives a power of over 90% with only 90 participants in each arm of the study. Considering 20% loss of follow up by 6 months total sample size required for this study will be 216.

**Inclusion criteria:**Diagnosed as type 2 diabetic patient according to WHO criteriaCurrently on oral Metformin monotherapy and able to afford cost for 6 months treatmentPatients with a personal mobile phonePatients who know how to retrieve/read SMS on mobile phone (Bangla with English alphabets)Willingness to receive SMS for 6 months at least one SMS per day.Patient registered with the BIHS health centre and lives in Dhaka City.Provide written informed consent and agree for a follow up visit after 6 months. (SMS reminders will be sent for the follow up visit).

**Exclusion criteria:**Patients with other types of diabetes, such as diagnosed as type 1 diabetes, gestational diabetes.Patients whose clinical condition might have interfered with the study such as mental illness, other serious illness or co-morbidities requiring hospitalization.Patients unable to give their informed consent or agree for follow up visit.Patients who do not own a mobile phone or cannot read SMS messages.Patients who reside outside Dhaka city.

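### The 20% loss allowance appears to be applied as × 1.2 instead of ÷ 0.8, so 216 randomised leaves about 86, not 90, evaluable per arm; power stays just above 90%

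*Protocol article*

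**What the plan says.** The Sample size section of the protocol article sets out the chain as follows.

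- Effect: "Assuming that standard care with metformin reduces HbA1c by 1% on average and the intervention adds another 0,5" percentage points, so the between-arm difference is 0.5.
- Variability: "Assuming a SD of 1, which seems reasonable".
- Power: "an alpha error level of 5%, the two-tailed calculation gives a power of over 90% with only 90 participants in each arm of the study".
- Attrition and total: "Considering 20% loss of follow up by 6 months total sample size required for this study will be 216".

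The Study type section divides the total into two arms of 108. The Data analysis section names the t-test for the primary outcome, the change in HbA1c. The article does not print the formula that leads from 90 per arm to 216. It describes no replacement of participants who are lost and gives no larger recruitment figure.

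**The concern.** An allowance for loss should make the number remaining after the loss equal to the number the power calculation needs. That means dividing by the proportion retained. Adding the loss percentage to the evaluable number always gives too few. The protocol's three figures (90 per arm, 20% loss, 216 in total) do not fit together, and 216 is what the additive shortcut produces.

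Readers will use this statement to judge whether a null result is informative. As it stands, it tells them that a 20% loss is covered with 90 per arm still in hand. A loss between 16.7% and 20% would look as planned and yet leave fewer than 90 per arm.

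**Working it through.** **Inputs.** Difference 0.5, SD 1, two-sided alpha 5%, 90 per arm, 20% loss and total 216 are from Sample size. The 108 per arm is from Study type, and the t-test is from Data analysis.

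**Step 1: reproduce the stated power.** For *n* per arm the noncentrality is (0.5/1) × √(*n*/2). At *n* = 90 this is 0.5 × √45 = 3.354.

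- Normal approximation: Φ(3.354 − 1.960) = Φ(1.394) = 91.8%.
- Noncentral t with 178 degrees of freedom: 91.6%.

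Both agree with the stated power of over 90%.

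**Step 2: reproduce the stated total.** The evaluable total is 2 × 90 = 180.

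- Additive shortcut: 180 × 1.20 = 216, an exact match.
- Division by the proportion retained: 180/(1 − 0.20) = 225. Per arm, 90/0.80 = 112.5, rounded up to 113, so 226 with equal arms.

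The shortfall is 9 randomised participants (10 with equal arms), about 4%.

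**Step 3: what 216 delivers at 20% loss.** 216 × 0.80 = 172.8, which is 86.4 per arm. In each arm 108 × 0.20 = 21.6 are lost, whereas only 108 − 90 = 18 can be lost if 90 are to remain.

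**Step 4: the loss that 216 does cover.** 1 − 180/216 = 16.7%.

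**Step 5: power at the numbers that remain** (difference 0.5, SD 1, two-sided 5%).

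| Evaluable per arm | Normal approximation | t-test |
|---|---|---|
| 90 | 91.8% | 91.6% |
| 86 | 90.6% | 90.3% |
| 85 | 90.3% | 89.99% |

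With the planned t-test, 86 per arm is the smallest equal-arm size that reaches 90%. Going from 90 to 86 per arm costs about 1.3 percentage points.

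**The case against.** **The power claim survives.** The protocol promises power above 90%, and 86 per arm gives 90.3%. A reader might infer from the arithmetic slip that the trial falls below its stated power, or that it must enrol more. The protocol's own inputs do not support either inference. This part of the objection stands in full and limits the point to a correction of the statement.

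**The × 1.2 step is inferred.** No formula is printed, and the article never says outright that 90 per arm will remain after losses. The total of 216 can also be reached correctly from 86 per arm: 86/0.8 = 107.5, rounded up to 108. That is true, but the protocol names 90 and not 86. On that route 90 would be the figure that does not belong, and the passage would still need correcting.

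**Fragility should not be overstated.** Two further readings are tempting.

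- *That loss just beyond 20% brings a real failure of power.* It does not. With 170 evaluable (85 per arm, a loss of 1 − 170/216 = 21.3%), power is 89.99%, one hundredth of a point under 90%.
- *That the slip is what exposes the trial to an SD above 1.* That sensitivity is mostly a separate matter. Even with a full 90 per arm, power drops below 90% at an SD of about 1.03, and at an SD of 1.05 it is 88.8% with 90 per arm against 87.4% with 86. Correct inflation would not remove it.

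**Conclusion.** The point holds as a minor error in the sample-size statement. The 20% allowance appears to have been added to 180 when 180 should have been divided by 0.8. The total of 216 therefore yields about 86 evaluable per arm at the planned loss, and keeps 90 only up to 16.7% loss. The power conclusion is still true, though barely: 90.3% in place of 91.6%.

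This rests on the protocol's difference of 0.5 and SD of 1, on equal loss in the two arms, and on participants lost to follow-up contributing no 6-month HbA1c. That the factor 1.2 was used is inferred from the exact match with 216. The inconsistency among the three stated figures does not depend on that inference.

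**What to change.** Keep 216 and replace the attrition sentence in Sample size with wording such as:

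> With 216 randomised and 20% loss, about 86 per arm are evaluable, giving about 90% power for a 0.5% difference with SD 1; 90 per arm is retained only if loss is at most 16.7%.

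The cost is one sentence and a slightly less favourable figure. Recruitment, allocation, endpoint and analysis stay as they are. If the sponsor wants 90 evaluable per arm at 20% loss, the matching total is 226 with equal arms, but the stated power does not require it.

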### Randomization

All the study participants will be randomized to receive either the standard care or mobile phone SMS interventions plus standard care. A central computer generated randomization list with patient ID numbers will be generated. Data collection and laboratory assays will be done by investigators masked to intervention allocation; however, study participants cannot be masked as they will receive the SMS intervention (Figure 1).

### Data collection and intervention

Data will be collected at baseline (0 month) and after 6 months through questionnaires, physical measurements and blood tests (Figure 1). We will send out mobile phone SMS to patients in the intervention group for medication reminders and health education about diabetes, its complications, diet and physical activity. SMS content has been developed using different national and international guidelines for diabetes and will be field tested for clarity and contents. The patients will be encouraged to send messages/call the study team for any queries encountered in response to the text messages. The study team will then call patients who had a problem within 2 working days. Study staff will maintain a study register to record all SMS responses and other mobile phone communications with patients in a study log.

### SMS development and testing

The SMS messages were developed by a team comprising of general physicians, an endocrinologist, an epidemiologist, a nurse and a undergraduate student. After developing the SMS messages in Bengali, we sent these messages to several individuals in the pre-test stage including persons who can only read SMS and have no formal education qualifications. After receiving the feedback, we tried to make the contents of the SMS suitable for the general population. We will ensure that all our participants in the study can read the SMS messages by themselves or someone in the family who can describe the messages to them if they do not understand. At the end of the follow-up we will evaluate if they failed to understand any of the SMS.

*Most of the 90 SMS were developed based on the principles of behavioural learning theory and transtheoretical model of behavioural change* [17-19]. *All participants in the SMS intervention group will receive the 90 SMS randomly, once a day over the 6 months period. Some examples of the SMS are provided below:*Diabetes is a serious disease, but it can be easily controlledCheck your blood pressure at least for 2 times in a year and write it downRegular physical exercise or walking habit will help to bring your blood glucose to normal levelDon't forget to take your medication as advised by your physicianA planned diet and weight control will help to reduce the risk of heart disease and strokeDo you have any appointment with your doctor in this month? Then do not miss it.Have you done your physical activity, walking for 30 minutes or exercise today? If not then do it when you become freeIf you are stressed, stop your work. Go for a walk and relax!A healthy diet will keep you healthy and happyDid you take all your medication today as advised by your physician?Visiting your doctor timely is essential for youDiscuss with your doctor about your concerns and worries about your conditionAwareness about your disease and following your doctor's advice can make your life healthy and happyTaking medication timely will help to keep your blood sugar in control and avoid complicationsDiabetic people with disciplined life enjoys a healthy longer life.

We will attempt to replicate interview and physical measurements in a random sub-set (~5%) of the sample to evaluate repeatability. For repeatability studies, we will have about 40 participants with duplicate measures which will be sufficient to estimate kappa coefficients of agreement of inter and intra-observer reliability with a high degree of precision even for categorical variables.

### Quality monitoring and assurance

Data collection forms will be checked on a daily basis by a Research Fellow to ensure complete and accurate data entry by field staff. Cross checking of data collection forms will be performed in the field by the data collectors for inconsistency and missing data. The Principal Investigator (PI) will carry out periodic data checks and look for systematic patterns, errors, scheduling problems or incomplete forms. Every week when the team meets, the PI will pick 2 questionnaires filled in the current week by one interviewer. The PI will go through the questionnaire, question by question with the entire team, to identify incomplete/missing entries and any errors as to rectify and clear any doubts by the interviewers.

### Primary outcome measures

[Time Frame: 6 months]Disease progression (HbA1c level).

The primary analysis will be intention to treat which will provide relative unbiased comparisons among the intervention and control groups. It will also reduce the effects of crossover and dropout, which may break the random assignment to the treatment groups in a study.

### Secondary outcome measures

[Time Frame: 6 months]Diabetes knowledge (questionnaire)Self-reported medication adherence (Questionnaires)Clinic attendance (Clinic registers and questionnaires)Quality of Life (Self-reported questionnaires)Cost effectiveness of SMS interventions in reducing HbA1c

Description of outcome variables:Socio-demographic and economic information: Data on participant’s age, sex, religion, education, marital status, occupation, income, family size, family income, objects ownedMobile phone use and habits: Owns mobile phone, years of using mobile phone, can read SMS, can send SMS, frequency of sending SMS, monthly expenses for mobile phone and SMS, willingness to pay for SMS health advice/ medication reminder, maximum amount for mHealthKnowledge of prevention, management and complications of diabetes: Levels of knowledge and perceptions of diabetics, Risk Factors for diabetes, knowledge about prevention, management and complications of diabetes.Self-perceived Quality of Life Assessment: We will use EQ-5D tool and other modified tools to assess the Quality of Life for all participants. This questionnaire has been tested and validated to capture the difference in quality of life in chronic diseases patients.Self-reported diseases or disease prevalence: Self -reported information on different diseases and physical disability by the study participants.Medical History: Any known history of diabetics, CVD, hypertension, cancer, hypercholesterolemia, stroke, kidney diseases, other vascular disease, major surgery.Family history of diseases: Family history of diabetes, hypertension, heart diseases, stroke, kidney diseases, cancerMedication history: List of current and past medication taken by the patient, medication for diabetes, average monthly expenditure for medication, transportation to health facility/physician and consultation.Medication adherence: We will data on medication adherence of participants using different standardized tools and modifying to local context.Health seeking behaviour: Data will be collected on type of doctor visited during the past year, number of visits, distance travelled for consultation and expenditure for health.Tobacco Use (WHO modified questionnaire): A modified WHO questionnaire on use of different forms of tobacco currently and in the past with expenditure will be recorded.Physical Activity (GPAQ): WHO modified GPAQ questionnaire which has been validated in the fields will be used to capture information on different forms of physical activityDiet (WHO IMS/ Food Frequency Questionnaire): A modified and validated food frequency questionnaire will be administrated to ascertain food consumption pattern and dietary choices, type and frequency of consumption of different foods.Mental health status (PHQ9): The Patient Health Questionnaire PHQ 9 which is a standard tool for collecting mental health status in primary health care setting will be used.Life events and Disability: Life events related questions like new job, marriage, separation, injury, accident will be asked, which will be based on validated questionnaire.Anthropometric Measurements: Weight, Height, Mid-Upper Arm Circumference (MUAC), Waist and Hip circumference, Blood Pressure (BP), Pulse rate.Biological tests: Blood tests for HBA1C will be performed.

A standard operating procedure (SOP) will be developed for questionnaire administration, physical measurement, SMS, biological sample collection, transport and storage. Medical history and family history will be obtained through a face-to-face interview using structured questionnaire. The medication use will be recorded from patient's medication book that is maintained by all registered patients. The duration of diabetes, duration of hypertension and complications will be collected from patient medical records maintained by BIHS physician, review of the patient’s file and investigations.

### Data analysis

Data coding, quality control and data entry will be done following established procedures at the International Center for Diarrhoeal Diseases Research, Bangladesh (icddr, b). Precoded questionnaire will be used to minimize data coding errors. All data forms and questionnaires will be checked for errors and necessary corrections will be made before data entry. A data entry programme with built-in range and consistency checks will be used. Frequency distributions will be run to identify outliers. In all analyses, potential confounding variables and effect modifiers will be considered.

Basic presentations of data will include number and percentages of cases with diabetes by age, sex, location of residence, and in relation to different known risk factors. Chi-square tests will be used to assess the association between diabetes and risk factors. Prevalence odd ratios will be calculated for diabetes adjusted for major confounding variables (e.g. age, sex, smoking habits, socioeconomic status, nutritional status, family history of diabetes). Interaction between age and risk factors, obesity and diabetes risk factors, and nutritional status and risk factor (hypertension and diabetes risk factors) will also be examined in the logistic regression model.

Effect of intensive mobile phone SMS intervention will be examined by comparing the longitudinal change in glycated hemoglobin (HbA1c) level changes between intervention and control groups. The change in HbA1C will be defined as the difference between mean HbA1c at the first survey and minus that at the second survey and standardized for the time between surveys. We will analyze the primary outcomes with the t-test. The primary analysis will be intention to treat which will provide relative unbiased comparisons among the intervention and control groups. It will also reduce the effects of crossover and dropout, which may break the random assignment to the treatment groups in a study. Relative risk (RR) will be reported for non-adherence, with an RR less than 1 suggesting better outcome for the intervention group. As a measure of absolute effect size, we will also calculate the number needed to treat (NNT) and its associated 95% CI for both unadjusted primary outcomes. Adjusted analyses by fitting a logistic regression model to the primary outcomes with adjustments for sex, age, baseline HbA1c level will be performed.

Secondary outcomes will be compared with the χ2 test for categorical outcome. Fisher's exact test for outcomes will be used to estimate p values. Logistic regression will be used for Quality of Life (QoL) and other continuous variables. In the subgroup analysis in the intention-to-treat population, we will compare the intervention groups within each subgroup of patients with the χ2 test for the categorical outcome and logistic regression for QoL. For all models, the results are expressed as an estimate of effect size, with 95% CIs and p values. The response type throughout the study period will be analysed by categorising time since random allocation to the 6 months and doing a χ2 test between time and response type. All statistical analyses will be done using SPSS version 20 (IBM Corporation, USA).

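### The risk-factor analyses take diabetes as the outcome in a sample where everyone has it; separately, the subgroup comparisons do not test whether the SMS effect differs between subgroups

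*Protocol article*

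**What the plan says.** **Who is in the trial.** The inclusion criteria, printed under Sample size in the protocol article, require a diagnosis of type 2 diabetes by WHO criteria. The exclusion criteria remove "Patients with other types of diabetes, such as diagnosed as type 1 diabetes, gestational diabetes". Study type describes two arms of 108, both made up of such patients. No comparison group without diabetes is described.

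**The risk-factor analyses.** Data analysis first describes the sample, then states that "Chi-square tests will be used to assess the association between diabetes and risk factors" and that "Prevalence odd ratios will be calculated for diabetes adjusted for major confounding variables". It goes on to "Interaction between age and risk factors, obesity and diabetes risk factors, and nutritional status and risk factor", to be examined in the logistic regression model.

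**The treatment effect.** A separate paragraph covers the SMS effect on HbA1c: a t-test, plus a logistic model adjusted for sex, age and baseline HbA1c.

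**Effect modification and subgroups.** One general sentence reads "In all analyses, potential confounding variables and effect modifiers will be considered". The stated subgroup method, to be applied by intention to treat, is that "we will compare the intervention groups within each subgroup of patients with the χ2 test for the categorical outcome and logistic regression for QoL". The subgroups are neither named nor counted. The section adds that results of all models will be given as effect sizes with 95% CIs and p values.

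**The concern.** There are two separate problems.

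First, an association between diabetes and a risk factor needs people with and without diabetes. This sample has only the former. The wording would suit a cross-sectional prevalence survey, and here that part of the plan can produce no result.

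Second, setting one subgroup's p value beside another's does not answer whether the intervention works differently in the two. Smaller subgroups have lower power. One can therefore cross 5% and the other miss it when the true effect is the same in both. Research objectives says the results are meant to inform policy-makers, and a chance pattern of this kind could be taken as guidance on whom to send messages to.

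**Working it through.** **1. Can the risk-factor analyses be estimated?**

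Put diabetes = 1 for all 216 participants and split them by any binary risk factor, here 100 exposed and 116 unexposed for illustration.

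- Chi-square: expected count = row total × column total / N. The no-diabetes row total is 0, so both its expected counts are 0 and the statistic is undefined.
- Odds ratio: (100 × 0)/(116 × 0) = 0/0.
- Logistic model: with every outcome equal to 1, the log-likelihood is the sum of log(pᵢ). It rises towards 0 as the intercept goes to infinity, whatever the slopes, so there is no finite maximum and interaction terms are not identified.

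A numerical check agreed. A logistic fit with 216 outcomes of 1 and one simulated covariate did not converge and was flagged as perfect separation. The standard errors were about 2.9 × 10⁷ (intercept) and 1.2 × 10⁶ (slope). The chi-square routine stopped on a zero expected count.

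**2. How misleading can within-subgroup comparisons be?**

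Inputs from Sample size: difference 0.5, SD 1, two-sided 5%, 90 evaluable per arm, 20% loss, total 216. The subgroup split is an assumption. The HbA1c scale is used because the protocol gives no effect size for its categorical outcomes or QoL.

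The plan's own figures come first. Power = Φ(0.5 × √(n/2) − 1.96). At n = 90 this is Φ(3.354 − 1.96) = 0.918, so the stated power of over 90% reproduces. The total reproduces as 180 × 1.2 = 216.

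Now let the SMS effect be 0.5 in everyone. With powers p₁ and p₂ in two separate subgroups, the chance that exactly one is significant is p₁(1 − p₂) + p₂(1 − p₁).

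| Split (assumed) | n per arm in each subgroup | Power in each | Exactly one significant |
|---|---|---|---|
| 50:50 | 45, 45 | 0.660, 0.660 | 0.449 |
| 30:70 | 27, 63 | 0.451, 0.801 | 0.529 |
| 20:80 | 18, 72 | 0.323, 0.851 | 0.624 |

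If 20% are lost from 108 per arm, 108 × 0.8 ≈ 86 remain, or 43 per arm in each half. The t-test power is then 0.630, and 2 × 0.630 × 0.370 = 0.466. The 50:50 figure is therefore about 45-47%. With no effect at all it is 2 × 0.05 × 0.95 = 0.095.

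**3. What would an interaction term deliver?**

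At 50:50 with 45 per cell, the interaction contrast has SE = 1 × √(4/45) = 0.298.

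- 95% CI half-width: 1.96 × 0.298 = 0.58.
- Power for a 0.5-point difference in effect: Φ(0.5/0.298 − 1.96) ≈ 0.39.
- Difference detectable with 80% power: (1.96 + 0.842) × 0.298 ≈ 0.84.

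The interaction addresses the right question, but imprecisely.

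**The case against.** Several counter-arguments have force.

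- *The diabetes paragraph is descriptive.* A reader might infer that it is the plan's effect-modifier analysis, and fault its interactions for leaving out the trial arm. The text does not support that. The paragraph opens as basic data presentation, and the SMS effect has its own paragraph. What stands is only that these analyses cannot be run.
- *Interaction terms may be in an unseen SAP.* A reader might infer that the trial will never estimate whether the SMS effect differs between patients. The article does not establish this. It says effect modifiers will be considered, no objective or hypothesis concerns differential effects, and such detail commonly sits in a SAP. The point rests instead on the subgroup method that the article does state.
- *The protocol sets no rule that declares a subgroup positive, and it promises effect sizes with CIs.* This is true, so conclusions that SMS works in one subgroup and not another are a risk and not a planned step. Still, separate intervals compared by eye give no estimate of the difference in effect.
- *The percentages are not for the planned tests.* This is also true. The stated subgroup tests concern categorical outcomes and QoL, and no split is given. The figures show how the problem arises and how large it can be on one scale; they do not predict the trial's own subgroup results.

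On the other side, the constant outcome follows from the trial's own eligibility criteria. It is a misstatement, not a detail left out.

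**Conclusion.** Both parts hold, within limits. The chi-square tests and adjusted prevalence odds ratios for diabetes cannot be estimated, and this needs no assumption beyond the eligibility criteria. The interaction models fail for the same reason if their outcome is diabetes. That is the natural reading, because the sentence follows directly on the prevalence odds ratios and names no other outcome.

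The subgroup method does not test whether the SMS effect differs. Under an identical effect, exactly one of two subgroups is significant in roughly 45% to 62% of trials, depending on the split, and in 9.5% with no effect. These figures assume a two-level subgroup, the HbA1c scale, a difference of 0.5 and SD 1.

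A reader might infer that the main result is compromised. It is not: the randomised HbA1c comparison by t-test and its sample size do not depend on either analysis.

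**What to change.** 1. In Data analysis, delete the chi-square tests, prevalence odds ratios and risk-factor interactions that take diabetes as outcome. If a risk-factor analysis is wanted, restate it with an outcome that varies in this sample, such as baseline HbA1c.
2. Keep the categorical outcomes and QoL in the subgroup analysis, but add an arm-by-subgroup interaction term in a model suited to each outcome. Limit this to a few subgroups named in advance; sex, age and baseline HbA1c are already listed as adjustment variables.
3. Add HbA1c change to the subgroup analysis through a linear model with the same interaction term.
4. Report each interaction estimate with its 95% CI, labelled exploratory. Give within-subgroup estimates as description only.

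The first change is deletion or rewording. The others are more than wording: they add models, including a linear one for HbA1c that the article does not now contain. They need no new data. The interaction will have low power (about 39% for a 0.5-point difference at an assumed 50:50 split), so a non-significant result must not be read as evidence of a uniform effect.
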